### Interim analyses {21b}

No interim analyses are planned. Considering the high curability and safety of FCM-ESD and SCM-ESD reported in the previous studies and our pilot study, patients would not be seriously disadvantaged by completing the study without an interim analysis [19].

### Methods for additional analyses (e.g., subgroup analyses) {20b}

As for subgroup analysis, primary outcomes and some secondary outcomes, including the number and time of hemostasis with hemostatic forceps and total procedure time, will be analyzed according to the tumor location, tumor size, antithrombotic agent use, experience of ESD, and pathological ulceration.

### Method in analysis to handle protocol non-adherence and any statistical methods to handle missing data {20c}

The analysis will be performed primarily on the largest population of enrolled patients, excluding those who do not receive trial treatment, those with serious ethical guideline violations, and those with missing primary outcome data. In principle, missing data will not be imputed because it is assumed that there will be quite few missing data due to the design of this trial.

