### Outcomes {12}

The primary outcome is successful completion of ESD using an electrosurgical knife alone, which is considered an important indicator reflecting the hemostatic ability to control intraoperative bleeding. If hemostatic forceps are required as a rescue device to achieve hemostasis prior to tumor retrieval, the procedure will be considered a failure. Secondary outcome includes the number and duration of hemostasis performed with hemostatic forceps; procedure time, including total ESD time, mucosal incision time, and submucosal dissection time; speed of submucosal dissection; en bloc resection rate; complete resection rate; curative resection, evaluated based on endoscopic curability (A or B); degree of each endoscopic curability category; thickness of the submucosal layer in the resected specimen; type and volume of submucosal injective solution used; occurrence of operator change; and adverse events. Total ESD time is divided into mucosal incision time and submucosal dissection time. The continuous outcome data will be analyzed without any categorization.

Outcome without histopathological assessments will be evaluated at ESD. Outcomes with histopathological assessments including complete resection rate; curative resection, evaluated based on endoscopic curability (A or B); degree of each endoscopic curability category; and thickness of the submucosal layer in the resected specimen will be evaluated within 1 week after ESD.

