### Plans to promote participant retention and complete follow-up {18b}

Upon registration, all assessments of study outcomes and follow-up will be conducted during the hospital stay. Furthermore, follow-up on procedure-related adverse events will be continued for six months after treatment. The principal investigator will continuously monitor the retention rate.

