## Statistical methods

### Statistical methods for primary and secondary outcomes {20a}

With regard to the primary outcome as the completion of ESD with the knife alone, the two groups will be compared using the Cochran-Mantel–Haenszel test stratified by lesion location (upper or middle third of the stomach vs. lower third of the stomach), lesion size (0–20 mm vs. 21 mm or more), and presence of antithrombotic agents (continued, discontinued, or not administered). If SCM-ESD significantly outperforms FCM-ESD (two-sided significance level of 5%), we will conclude that SCM-ESD is a more useful treatment method than FCM-ESD.

With regard to secondary outcomes, the number and duration of hemostasis using hemostatic forceps and procedure time will be analyzed using the Wilcoxon rank-sum test. The speed of dissection, thickness of the submucosal layer in the resected specimen, and volume of the submucosal injection solution will be analyzed using *t*-tests. En bloc resection, complete resection, curative resection, severe thermal damage to the resected specimen, type of submucosal injection solution, operator change, and occurrence of adverse events will be analyzed using Fisher’s exact test.

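### The one analysis population stated in the article drops treated patients whose primary outcome is missing and makes no exception for the adverse-event comparison

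*Protocol article*

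**What the plan says.** Section {20c} of the protocol article sets the population: "The analysis will be performed primarily on the largest population of enrolled patients". Three groups are then taken out of it, and the article words this rule as "excluding those who do not receive trial treatment, those with serious ethical guideline violations, and those with missing primary outcome data". It adds that missing values will in principle not be imputed, because "it is assumed that there will be quite few missing data due to the design of this trial".

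The Outcomes section {12} lists "occurrence of operator change; and adverse events" among the secondary outcomes. The statistical methods section {20a} says that "operator change, and occurrence of adverse events will be analyzed using Fisher’s exact test". Neither section names a population for adverse events.

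The Outcomes section defines the primary outcome as successful completion of ESD with the knife alone. It scores the procedure as a failure if hemostatic forceps are needed for hemostasis before the tumor is retrieved. On timing it says: "Outcome without histopathological assessments will be evaluated at ESD".

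Safety data are collected independently of any analysis set. The retention section {18b} says that "follow-up on procedure-related adverse events will be continued for six months after treatment", and the harms section {22} requires recognized events to be documented and serious ones reported.

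**The concern.** Whether a patient's knife-alone completion was recorded has no bearing on whether that patient was exposed to the procedure and harmed by it. A population conditioned on having the primary outcome may be defensible for efficacy. Applied to adverse events, it makes the harms comparison depend on an efficacy variable.

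The exclusion could also be informative. If an ESD is stopped early because of a complication, that complication may be the reason no completion result is entered, so the rule would remove the event together with the patient. The trial is open-label and investigators enter the outcome data ({17a}, {18a}), so a decision to code such a case as missing would be made with the arm known.

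The Discussion counts adverse events among the outcomes meant to show the advantages of the spray mode, and it foresees adoption of that mode as the preferred method. With about 65 patients per group and possibly few events, one or two omitted patients would be visible in the harms table.

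**Working it through.** **1. Which population applies to adverse events?** {20c} speaks of the analysis in general and does not restrict itself to the primary outcome. {12} makes adverse events a secondary outcome, and {20a} assigns them Fisher's exact test without a population. Taken together, the only stated population governs the adverse-event test.

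**2. Which treated patients can leave it?** Untreated patients are no issue for safety. Two grounds remain: missing primary outcome, and serious ethical guideline violation. The second may reflect invalid consent or data that may not be used, which is a legitimate reason to exclude a patient from every analysis. The first is the problem.

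**3. When could the primary outcome be missing in a treated patient?**
- *Bleeding the knife cannot control.* The intervention description {11a} sends this to hemostatic forceps, and {12} scores such forceps use before retrieval as failure. The outcome is present and the patient stays in.
- *En bloc resection not feasible.* {11a} provides for piecemeal resection or ablation. The procedure goes on and forceps use can be recorded.
- *Perforation.* {11a} allows a change of operator and does not name perforation as a reason to abandon the procedure.
- *ESD stopped before retrieval without forceps use.* This is not completion, but it does not meet the stated failure condition either. {12} does not explicitly classify it, so it could be coded as failure (patient stays in) or as missing (patient and any event leave the comparison).

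Only the last case, or a plain recording gap, triggers the problem.

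**4. Size.** The article gives neither an adverse-event rate nor a count of exclusions, so no figure can be derived from it. The one usable input is the planned group size of 65, from the Sample size section. The 62 per group behind it reproduces (pooled chi-square, 34.6% vs 59.6%, two-sided 5%, 80% power). For 5% dropout, 62/0.95 = 65.3, against the stated 65. The point does not rest on this calculation.

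One event is 1/65 = 1.5 percentage points. The counts below are assumed, for illustration only:

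| Assumed counts, all started | Difference | After dropping patients with events | Difference |
|---|---|---|---|
| 3/65 (4.6%) vs 1/65 (1.5%), p = 0.62 | 3.1 points | one from the first arm: 2/64 (3.1%) vs 1/65 (1.5%), p = 0.62 | 1.6 points |
| 3/65 (4.6%) vs 1/65 (1.5%), p = 0.62 | 3.1 points | one from the second arm: 3/65 (4.6%) vs 0/64 (0%), p = 0.24 | 4.6 points |
| 6/65 (9.2%) vs 0/65 (0%), p = 0.028 | 9.2 points | three from the first arm: 3/62 (4.8%) vs 0/65 (0%), p = 0.113 | 4.8 points |

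The p values are from Fisher's exact test. Rows 1 and 2 show that a single dropped patient can shrink or widen the observed difference. Row 3 needs three such patients in one arm, which is a lot for an outcome seen during the procedure. With no such exclusions, nothing changes.

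**The case against.** The strongest reply is that the article says the analysis will be done *primarily* on this population, which leaves room for others. A safety set is ordinary content for a full protocol or SAP, neither of which is shown. This stands against a reader who infers that no safety set exists, or that this is the only one: the article shows only that it is the one set stated. It does not remove the point. The article chose to state its exclusions and tied one of them to the primary outcome without limiting it to efficacy, so a safety set of all treated patients defined elsewhere would depart from that sentence.

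A reader might also infer that harms go uncounted. The documents do not support that. Events are documented, serious ones are reported, procedure-related events are followed for six months, and the auditing section {23} has adverse events reviewed monthly. What can be lost is a patient's place in one between-group comparison.

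Nor is uncontrolled bleeding an example, because the forceps rule gives that patient a failure and keeps the patient in. On a natural reading, an abandoned ESD is simply not completed, which would close most of the remaining gap. That reading is sensible but is not written down.

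Finally, missing data should indeed be few for an outcome observed at the procedure, and ethical violations can be a sound ground for exclusion. Both limit the size of the point, and the second limits the fix.

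**Conclusion.** The point holds in a narrow form. As written, the stated population conditions the adverse-event comparison on the availability of the primary outcome, and no exception is made. It matters only if some patient has ESD started and ends without a recorded primary outcome, most plausibly when a procedure is stopped without forceps use and is coded as missing.

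The effect is likely small, and the article supports no estimate of it. The direction is unknown, so a reader should not conclude that the rule understates harm from the spray mode: the same exclusion in the forced-mode arm would act the other way. The illustrations assume 65 per group and invented event counts. The case for a change rests on the mismatch between the exclusion and the purpose of a safety comparison, and on how little the change costs.

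**What to change.** In {20c}, limit the missing-primary-outcome exclusion to the efficacy analyses. Add that adverse events are analysed in all patients in whom ESD was started, by allocated mode, whether or not the primary outcome is available, and that any conversion between modes under {11b} is noted alongside. Keep the exclusion of patients whose data may not be used for ethical or consent reasons.

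In {12}, state that an ESD started but not completed counts as a failure on the primary outcome and not as missing.

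The cost is two or three sentences. No new data are needed, because the events are already being collected; recruitment has ended, but this is an analysis rule. The downside is that the safety and efficacy denominators may differ by a few patients, which a line in the participant flow can explain.

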### Plans to give access to the full protocol, participant-level data and statistical code {31c}

The datasets analyzed in this trial, statistical codes, and full protocol will be available from the corresponding author upon reasonable request.

## Oversight and monitoring

### Composition of the coordinating center and trial steering committee {5d}

The coordinating center is comprised of experts in gastroenterology and endoscopy. They are responsible for overseeing the trial and managing the protocol and trial-related documents. The trial steering committee is composed of members, including principal investigators from each institution. They are responsible for the overall management of the trial and implementation of the protocol at each institution. Meetings will be held once a month to discuss protocol compliance and any changes to the protocol.

### Composition of the data monitoring committee, its role and reporting structure {21a}

Members of the data monitoring committee are responsible for verifying the progress of the trial and ensuring that it is conducted, recorded, and reported in accordance with relevant laws, guidelines, and study protocols. The committee members are independent of the clinical trial stakeholders and are not involved in patient registration or treatment.

### Adverse event reporting and harms {22}

When an adverse event is recognized, the investigator must promptly take appropriate measures and document the event in the medical records or other relevant documents. If the trial treatment is discontinued or if treatment for an adverse event is required, the patients must be informed accordingly.

The reporting procedures are as follows: (i) in the event of a serious adverse event, the investigators must take necessary measures including explaining to the patient and promptly report it to the principal investigator, following the “Procedure Manual for Handling Safety Information in Human Medical Studies”; (ii) when being aware of a serious adverse event, the principal investigator should promptly take necessary measures, ensure appropriate responses, and create a “Serious Adverse Event Report,” and submit it to the hospital director through the secretariat of the Clinical Trial Ethics Revie Committee. Furthermore, the principal investigator should promptly share information related to the occurrence of adverse events with other trial investigators.

### Frequency and plans for auditing trial conduct {23}

The project management group will meet once a month to review the trial. The meeting will include a review of registration, consent procedures, protocol adherence, adverse events, and quality of control of all data. The trial steering group and the independent data monitoring and ethics committee will meet to review conduct throughout the trial period once per 6 months.

### Plans for communicating important protocol amendments to relevant parties (e.g., trial participants, ethical committees) {25}

If any protocol modifications are required, they are submitted to the IRB for approval prior to implementation. A revised copy will be stored, and the protocol in the clinical trial registry will be updated. This study is an investigator-initiated clinical trial with no trial sponsor. The principal investigator will be communicated to all study personnel including investigators in each institution on time. Participants will also be informed orally or in writing of any amendments to the protocol.

### Dissemination plans {31a}

The findings of this trial will be presented at domestic and international conferences and disseminated through the publication of papers in peer-reviewed journals. No personally identifiable information will be included during this process.

## Discussion

This trial aims to provide evidence supporting the superiority of hemostatic ability in SCM-ESD compared with FCM-ESD for patients with intramucosal EGN. Completion of ESD with the knife alone, without the use of hemostatic forceps as the primary outcome measure, can be achieved when bleeding control using the knife is sufficient during ESD. The higher completion rate in SCM-ESD indicates that the bleeding control ability using the knife is superior to that of conventional FCM-ESD. The number and duration of hemostasis with hemostatic forceps, as secondary outcomes, also reflect the hemostatic ability of the knife during ESD. If bleeding control with the knife is better, the number and duration of hemostasis with hemostatic forceps can be expected to decrease, even when needed. Additionally, other secondary outcome measures, such as procedure time, en bloc and complete resection rates, and adverse events, will provide a comprehensive understanding of the potential advantages of SCM-ESD over FCM-ESD.

In conclusion, the findings of this multicenter randomized controlled trial are expected to provide valuable evidence on the hemostatic efficacy of SCM-ESD compared with FCM-ESD in patients with intramucosal EGN. These results could lead to the adoption of SCM-ESD as the preferred treatment method for EGN, potentially improving the safety and reliability of ESD procedures.

## Trial status

Recruitment for this RCT began April 4, 2022, and the first participant was enrolled on April 5, 2022. We initially planned for recruitment to end on March 31, 2024 (24 months). However, owing to the rapid pace of case accumulation, recruitment was completed ahead of schedule on February 21, 2023. Follow-up on procedure-related adverse events is continued. Study protocol data: initial approval, March 23, 2022; current version approval, August 25, 2022.

## Data Availability

The final datasets will be available from the corresponding author upon reasonable request after completion of the study.

## Abbreviations

ESD: Endoscopic submucosal dissection
EGN: Early gastric neoplasms
SCM: Spray coagulation mode
FCM: Forced coagulation mode
SCM-ESD: Spray coagulation mode endoscopic submucosal dissection
FCM-ESD: Forced coagulation mode endoscopic submucosal dissection
ER: Endoscopic resection
EMR: Endoscopic mucosal resection
HFU: High frequency unit
SPIRIT Standard protocol Items: Recommendations for Interventional Trials
UMIN-CTR: University Hospital Medical Information Network Clinical Trials Registration
IRB: Institutional Review Board
UMIN: University Hospital Medical Information Network
INDICE: Integrated Network of Clinical Research Information and Electronic Medical Records
RCT: Randomized controlled trial
SAE: Serious adverse event
